# An implementation intervention to increase the routine provision of antenatal care addressing gestational weight gain: study protocol for a stepped-wedge cluster trial

**DOI:** 10.1186/s43058-021-00220-y

**Published:** 2021-10-19

**Keywords:** Pregnancy, Weight, Physical activity, Nutrition, Antenatal, Implementation, Effectiveness, Stepped-wedge trial, Protocol

## Abstract

**Background:**

Weight gain during pregnancy that is outside of recommended levels is associated with a range of adverse outcomes for the mother and child, including gestational diabetes, pre-eclampsia, preterm birth, and obesity. Internationally, 60–80% of pregnant women report gaining weight outside of recommended levels. While guideline recommendations and RCT evidence support the provision of antenatal care that supports healthy gestational weight gain, less than 10% of health professionals routinely weigh pregnant women; discuss weight gain, diet, and physical activity; and provide a referral for additional support. This study aims to determine the effectiveness of an implementation intervention in increasing the provision of recommended gestational weight gain care by maternity services.

**Methods:**

A stepped-wedge controlled trial, with a staggered implementation intervention, will be conducted across maternity services in three health sectors in New South Wales, Australia. The implementation intervention will consist of evidence-based, locally-tailored strategies including guidelines and procedures, reminders and prompts, leadership support, champions, training, and monitoring and feedback. Primary outcome measures will be the proportion of women who report receiving (i) assessment of gestational weight gain; (ii) advice on gestational weight gain, dietary intake, and physical activity; and (iii) offer of referral to a telephone coaching service or local dietetics service. Measurement of outcomes will occur via telephone interviews with a random sample of women who attend antenatal appointments each week. Economic analyses will be undertaken to assess the cost, cost-consequence, cost-effectiveness, and budget impact of the implementation intervention. Receipt of all care elements, acceptance of referral, weight gain during pregnancy, diet quality, and physical activity will be measured as secondary outcomes. Process measures including acceptability, adoption, fidelity, and reach will be reported.

**Discussion:**

This will be the first controlled trial to evaluate the effectiveness of a implementation intervention in improving antenatal care that addresses gestational weight gain. The findings will inform decision-making by maternity services and policy agencies and, if the intervention is demonstrated to be effective, could be applied at scale to benefit the health of women and children across Australia and internationally.

**Trial registration:**

Australian and New Zealand Clinical Trials Registry, ACTRN12621000054819. Registered on 22 January 2021

Contributions to the literature
This is the protocol for the first controlled trial of an implementation intervention to support antenatal clinicians improve care for women for gestational weight gain.The implementation intervention will use innovative best-worst scaling methods to assess the priority barriers of clinicians and develop tailored implementation strategies specific to the needs of each sector.Data from approximately 5600 women will measure care-level outcomes to determine if the implementation intervention was successful. This will be supplemented by an assessment of cost-effectiveness, cost-consequence, and budget impact; diet, physical activity, and weight outcomes for women; and process measures including acceptability and adoption.These comprehensive outcomes will provide a robust assessment of the implementation intervention and its ability to change clinician’s practices to benefit the health of women and their babies. This will provide maternity services and policymakers with evidence to support such an intervention being supported for further scale-up.

## Background

Gestational weight gain (GWG) below or above-recommended levels is a leading risk factor for poor pregnancy outcomes, with the potential for harm to both mother and child [1]. For the mother, these include a higher risk of gestational diabetes [2], caesarean birth [1], greater postpartum weight retention, and greater risk of obesity long term [3–5]. For the baby, excess gestational weight gain is associated with a higher risk of macrosomia and neonatal morbidity [6].

To quantify an ideal gestational weight gain range, in 2009, the United States Institute of Medicine (IOM) developed total and trimester-specific incremental weight gain recommendations for optimal healthy weight gain during pregnancy based on a woman’s pre-pregnancy body max index (BMI) [7]. Guidelines in Australia [8] and other high-income countries [7, 9] recommend that antenatal care providers support women to gain weight within these recommendations. Internationally, most (60–80%) women gain weight outside of these recommended target ranges [1]. In Australia, 64% of pregnant women report gaining weight outside of recommendations [10], including 85% of pregnant Aboriginal Australian women [11]. A systematic review and meta-analyses of studies including over 1.3 million pregnancies found that of the women who gained weight outside of the IOM recommended ranges, 9.5–29% gained below and 37–73% above the recommended ranges [1, 12, 13].

Cochrane systematic review evidence shows that educational and behavioural interventions supported by weight monitoring are effective in reducing the risk of unhealthy gestational weight gain by 20% (average RR 0.80, 95% CI 0.73 to 0.87) [14]. Systematic review evidence also suggests that such interventions are most effective when delivered as part of routine antenatal care [15], and it has been reported that women prefer such care to be provided in a way that is person-centred and non-judgemental [16].

Consistent with this evidence, antenatal care guidelines in countries including Australia [8], Canada [17], New Zealand [18], and Ireland [19] recommend that antenatal care providers routinely (i) assess weight and gestational weight gain of all women at all antenatal visits; (ii) provide brief behavioural support to all women addressing weight gain, healthy eating, and physical activity; and (iii) offer referral to specialist services for support for weight gain, healthy eating, and physical activity, particularly for those women who are gaining weight outside their weight gain target.

Despite such guidelines, the provision of antenatal care supporting healthy gestational weight gain has been reported to be less than optimal [20]. For instance, in Canada, it has been reported that only 16% of health professionals (*N* = 508) routinely discuss a woman’s weight gain during antenatal visits, and just 28% and 46% discuss healthy eating and physical activity, respectively [21]. Additionally, a 2009–2010 secondary analysis of data from antenatal visits in the United States (U.S.) found that the majority of visits (59%; *N* = 120) included only one of five evidence-based elements of care related to weight, and no visit included all five [22]. Forty-nine per cent of women had their weight gain assessed, 85% received weight gain advice, 3% received assistance to achieve the recommended weight gain, and 11% had follow-up care arranged [22]. Similarly, of the 1454 women in a longitudinal cohort study in a hospital in North Carolina, USA, just over half (52%) reported receiving advice about gestational weight gain from their health care providers [23].

A variety of barriers impede the provision of recommended gestational weight gain care [20, 21], including forgetting to undertake assessments and care, inadequate knowledge of guidelines, concerns about women’s sensitivity to discussing weight, and lack of time, resources and referral sources, skill, and understanding of the need to provide such care [20, 24]. Systematic reviews suggest that a variety of strategies are effective in addressing such barriers to improving the provision of guideline-based care generally [25] and in maternity services specifically [26]. Such strategies include clinical leadership [27], systems and policies that support/prompt care delivery [28], clinician training [29–31], and audit and feedback of care delivery [26, 31, 32]. Across a variety of clinical settings, such strategies can result in a 5–20% improvement in the delivery of desired clinical practices [25]. Tailoring of these strategies to local barriers and local context through the use of theoretical implementation science frameworks and associated tools [33, 34] has been found to further aid the development of successful practice change interventions [35, 36].

There have been a small number of studies undertaken in single maternity services that have assessed the effectiveness of practice change strategies to improve the provision of weight-related care in pregnancy [37–41]. These controlled and uncontrolled trials used multiple evidence-based strategies including education and training, clinical supervision, local care guidelines, provision of clinical equipment and resources, and medical record prompts to support health professionals to support practice change [37–39, 41], with most testing a combination of clinician training, clinical equipment, and patient resources. However, only one applied a theoretical framework and conducted systematic barrier analysis and mapping as a basis for strategy development [41].

In addition, no studies have tested the effect of practice change strategies to enhance all elements of antenatal guideline care for gestational weight gain, that is, assessment of weight, provision of advice, and referral to support services [41]. Most existing studies have examined the effect of strategies on routine weight assessment only, provision of advice for gestational weight gain only, or both assessment and advice. For example, an Australian cohort study (*N* = 13,000 pregnancies) found that recording of weight improved through the provision of weighing scales and staff training (18.9%) and medical record prompts (61.8%) (*p* < 0.01) [41]. A U.S. cohort study of 733 clinicians that introduced medical record prompts also demonstrated an increase in recording of weight (*p* < 0.001) and GWG counselling (*p* < 0.001) [42].

Similarly, despite intervention cost-effectiveness and budget impact being a significant factor in health care decision-making [43], no economic evaluations of such implementation interventions have been reported [44]. Given these evidence gaps, a need and opportunity exist for rigorous trials to examine the effectiveness, efficiency, and affordability of implementation interventions designed to increase the provision of recommended antenatal care addressing gestational weight gain.

## Methods

See ‘Additional File 1’ and ‘Additional File 2’ for the CONSORT (stepped-wedge trial) and STARi checklists.

### Aim

The aim of this study is to determine the effectiveness of an implementation intervention in increasing the provision of recommended gestational weight gain care in antenatal appointments.

### Study design and setting

A stepped-wedge controlled trial will be conducted in maternity services in three health sectors within the Hunter New England Local Health District, New South Wales, Australia. As shown in Fig. 1, measurement of the outcomes will occur continuously via telephone surveys with weekly random samples of pregnant women who have attended the maternity services in the last 2–3 weeks, from 6 months prior to the delivery of the intervention in the first sector to 12 months after intervention completion in the last sector. Delivery of the 4-month implementation intervention in the three sectors will occur sequentially. The sequential delivery will provide pre- and post-intervention outcome data periods of variable lengths for each sector, with a minimum of 12 months post-intervention data to enable the assessment of the sustainability of the intervention effect. Intervention effect will be determined by comparing the prevalence of recommended care between the pre-intervention and post-intervention periods for the three sectors combined.

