**Fig. 1 Fig1:**

Data collection and intervention timeline for the stepped-wedge trial design

The stepped-wedge study design provides pragmatic and scientific advantages relevant to the conduct of complex implementation interventions in health services [32, 45]. First, such a design provides the same level of evidence as a standard parallel cluster controlled trial [46]. Second, the design addresses the practical difficulty of recruiting enough equivalent maternity services that would be required for a parallel cluster RCT and increases study efficiency by using each group as its own control [32, 45]. Third, the design provides an opportunity for all participating services to receive the intervention, providing motivation for clinician engagement. Finally, such a design demonstrates the feasibility of the intervention in an operational environment, a key determinant of the intervention being translated into routine practice elsewhere should it prove successful [45].

In Australia, public maternity services are a key setting for the provision of antenatal care to address gestational weight gain as they provide care for 55% of all birthing women, including care for a diverse range of population groups, including those with a high prevalence of risk and those who are disadvantaged [47, 48]. The maternity services involved in this trial provide care to approximately 7000 women annually across urban and rural areas, accounting for almost 70% of women birthing in public hospitals within the health district [46].

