### Participant blinding

Study personnel involved in collecting the outcome data will be blind to the order of the delivery of the implementation intervention across the sectors. Participants providing outcome data will not be informed of the experimental nature of intervention implementation across services and therefore will be blind to the stage of intervention occurring in the service they attended. Given the practice change nature of the intervention, clinicians in antenatal services will be aware when their service is in the intervention period.

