Each week, a sample of eligible women who have had an antenatal appointment in the past week (first appointment, 27–28 weeks gestation, or 35–36 weeks gestation) will be randomly selected via a computerised random number generator by members of the research team, none of whom will be involved in delivering antenatal care. Selected women will be mailed a participant information statement explaining the purpose of the survey one week prior to receiving a phone call inviting them to participate in the survey. Study posters will be displayed in antenatal clinics and flyers distributed in antenatal information packs provided at the time of the appointment. Based on cultural advice, women identified via the medical record data as being of Aboriginal or Torres Strait Islander origin and/or who are enrolled in an Aboriginal Maternal and Infant Health Service (AMIHS) will be first contacted by text message and invited to participate. If potential participants do not respond, they will be followed up with a telephone call 4 days later. Sampled women will have the opportunity to decline participation at any point, including opting out during the antenatal appointment or when they receive study information during their appointment, when they receive the study information letter in the mail, at the time of the phone call or text message, or partway through survey completion. On the morning of the day that contact is to be made via phone call or text message, medical record data will be checked, and any potential participants who are identified as having given birth or having had a negative pregnancy outcome will be deemed ineligible and not contacted.

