#### Implementation intervention delivery timeline

The implementation intervention will be implemented in each sector sequentially for 4 months prior to the follow-up data collection (Fig. 1). Given their organisational and system focus, all strategies, other than the dedicated Clinical Midwife Educator (CME), have the potential to continue to be implemented following the 4-month study intervention period, subject to the operational decisions of the local health district.

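### No random allocation of the sector order is described, yet parallel-trial evidence is claimed without condition and the stated model has no sector term

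*Protocol article*

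**What the plan says.** **Design.** Under Study design and setting: "A stepped-wedge controlled trial will be conducted in maternity services in three health sectors", and "Delivery of the 4-month implementation intervention in the three sectors will occur sequentially". Under Implementation intervention delivery timeline: "The implementation intervention will be implemented in each sector sequentially for 4 months prior to the follow-up data collection". Neither section says how the order of the sectors is set. The title, abstract and design section use the terms stepped-wedge, cluster and controlled; none calls the trial randomised.

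**Chance.** The only random mechanism described is the weekly sampling of women for the survey, who "will be randomly selected via a computerised random number generator by members of the research team" (Participant eligibility and recruitment, Pregnant women).

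**Order.** Apart from sequential delivery, order is mentioned under Participant blinding, where those who gather the outcomes are kept "blind to the order of the delivery of the implementation intervention across the sectors".

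**Claim.** In the design rationale after Fig. 1: "such a design provides the same level of evidence as a standard parallel cluster controlled trial". The next sentence says that the design "increases study efficiency by using each group as its own control".

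**Model.** Statistical analysis names a before/after indicator, a fixed effect for time and a random intercept for antenatal time point, with the three sectors combined. It names no sector or service term.

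**The concern.** In a stepped wedge, the first cluster to cross over supplies mostly post-intervention data and the last supplies relatively more pre-intervention data. If position is related to how well a sector already performs, or to how fast it is improving, part of that relation appears as an intervention effect. Two safeguards are usual. Random order makes the link between sector and position a matter of chance. A cluster term in the model compares each cluster with itself. The article describes neither, although its rationale relies on each group being its own control and its evidence statement carries no condition.

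At stake is how the pooled coefficient can be read: as a controlled estimate of the intervention effect, or as one mixed with sector differences of unknown size.

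**Working it through.** **Inputs from the protocol article**
- Three sectors, 4-month delivery in sequence, data from 6 months before the first start to 12 months after the last completion (Study design and setting).
- Data collection of 30 months (Pregnant women).
- Target increases of 15, 14 and 9 points for assessment, advice and referral (Sample size and power calculations).

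**Assumptions of this check**
- Steps run back to back.
- Each sector's own four delivery months are left out of the pre/post comparison.
- Sector-months have equal weight.
- Least squares is used on the percentage-point scale in place of the logistic model.
- The true intervention effect is zero, so any coefficient found is bias.

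**Step 1: timeline.** 6 + 3 × 4 + 12 = 30 months, which matches the stated duration and supports the back-to-back assumption.

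| Position | Pre months | Delivery months | Post months |
|---|---|---|---|
| First | 1–6 (6) | 7–10 | 11–30 (20) |
| Second | 1–10 (10) | 11–14 | 15–30 (16) |
| Third | 1–14 (14) | 15–18 | 19–30 (12) |

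This gives 30 pre and 48 post sector-months. The first sector supplies 6/30 = 20% of the pre data and 20/48 = 42% of the post data.

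**Step 2: level difference, no sector term (the model as worded).** Fit outcome = before/after + time to a layout in which one sector lies 1 point above the other two.
- *Monthly time effects.* Only months in which both states are observed inform the coefficient. These are months 11–14, when the first sector is post, the third is pre and the second is in delivery. The coefficient is therefore exactly the first sector minus the third: +1.00, 0 and -1.00 for an excess in position 1, 2 and 3.
- *Linear time.* +0.69, 0 and -0.69.

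As an illustration with assumed levels of +10, +5 and 0 points in positions 1, 2 and 3, the spurious effect is 0.69 × 10 = 6.9 points (linear) or 1.00 × 10 = 10.0 points (monthly).

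**Step 3: level difference, sector term added.** The bias is 0.00 in every position, with linear or monthly time.

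**Step 4: differing trends, sector term added.** Bias per 1 point a year of extra rise in one sector:

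| Position of that sector | Linear time | Monthly time |
|---|---|---|
| First | -0.28 | -0.41 |
| Second | +0.10 | +0.07 |
| Third | +0.18 | +0.34 |

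For an assumed 3 points a year, multiply by 3: about -0.8 to -1.2 if in the first sector, +0.2 to +0.3 if in the second and +0.5 to +1.0 if in the third.

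**Step 5: what a random draw does.** There are 3! = 6 orders, and each sector takes each position in two of them. The mean level bias is (0.69 + 0 - 0.69)/3 = 0 for linear time and (1.00 + 0 - 1.00)/3 = 0 for monthly time. The mean trend bias is (-0.28 + 0.10 + 0.18)/3 = 0 and (-0.41 + 0.07 + 0.34)/3 = 0. In any single order the bias is whatever that order gives.

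**The case against.** A reader might infer that the order is known to be non-random, or that it follows readiness, staffing or current performance. The documents do not support this. Sequential delivery describes any stepped wedge and fits a random order equally well, and no section gives a basis for the order. The article is condensed, it refers to a stepped-wedge CONSORT checklist in an additional file that is not at hand, and Fig. 1 is not visible. The method of allocation may be recorded elsewhere. So the finding is that no random allocation is described; it cannot be that none took place.

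A reader might also take the evidence statement as a claim of equality with a randomised trial. Its words are a parallel cluster controlled trial, and the article uses RCT separately in the following sentence. Nor does blinding the data collectors to order say anything about how the order arose.

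The strongest point concerns size. The 0.7 to 1.0 points per point of level difference comes from the missing sector term, and a sector term removes it in any order. A random draw alone would leave the realised trial exposed: a sector that differs from the other two falls in first or last position in four of the six orders. What is left for the order itself is small, rests on an assumed trend, and is negative when the first sector is the fast-improving one.

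These points limit the finding but do not remove it. The evidence statement is explicit and unconditional, and the article sets out the model's terms without sector.

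**Conclusion.** The point holds in a limited form. The article describes no random allocation of sector order, never calls the trial randomised, and still claims parallel-trial evidence without condition.

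- **Larger risk, from the model as worded:** about 0.7 to 1.0 points of bias for each point by which the first sector's level exceeds the others, and zero once sector is in the model.
- **Smaller risk, which a sector term does not remove:** about -0.8 to -1.2 points (first sector) or +0.5 to +1.0 points (last) for an assumed trend difference of 3 points a year. The largest of these, 1.2 points, is 1.2/9 = 13% of the referral target.

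The coefficients follow from the layout, given back-to-back steps, exclusion of delivery months and a linear scale. The sector differences they multiply are assumptions, because the documents give no sector-level rates or trends. The actual bias could therefore be negligible or substantial.

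**What to change.** 1. **Order.** In Study design and setting, state that one of the six orders is drawn at random before sector 1 starts, by someone not involved in delivery. This makes order-related bias zero in expectation; with three sectors it does not guarantee balance. The cost is one draw, and sectors cannot choose their slot.
2. **If the order is already fixed** (Trial status already gives a start date for sector 1), label the trial a non-randomised stepped wedge, state the basis for the order, and qualify or remove the equal-evidence sentence after Fig. 1. If the order was in fact drawn at random, one sentence saying so settles this part. Only wording changes.
3. **Model.** Add a sector fixed effect to the primary model in Statistical analysis, in line with the own-control rationale. This costs two parameters and possibly some precision. It complements the first change and does not replace it, because differing trends remain.
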